# Postoperative hepatic arterial chemotherapy in high-risk patients as adjuvant treatment after resection of colorectal liver metastases - a randomized phase II/III trial – PACHA-01 (NCT02494973)

**DOI:** 10.1186/s12885-018-4697-7

**Published:** 2018-08-06

**Keywords:** Colorectal cancer, Liver metastases, Liver resection, Adjuvant chemotherapy, Hepatic arterial infusion, Oxaliplatin, Randomized trial

## Abstract

**Background:**

After curative-intent surgery for colorectal liver metastases (CRLM), liver recurrence occurs in more than 60% of patients, despite the administration of perioperative or adjuvant chemotherapy. This risk is even higher after resection of more than three CRLM. As CRLM are mostly supplied by arterial blood flow, hepatic arterial infusion (HAI) of chemotherapeutic agents after resection of CRLM is an attractive approach. Oxaliplatin-based HAI chemotherapy, in association with systemic fluoropyrimidines, has been shown to be safe and highly active in patients with CRLM. In a retrospective series of 98 patients at high risk of hepatic recurrence (≥4 resected CRLM), adjuvant HAI oxaliplatin combined with systemic chemotherapy was feasible and significantly improved disease-free survival compared to adjuvant, ‘modern’ systemic chemotherapy alone.

**Methods/Design:**

This study is designed as a multicentre, randomized, phase II/III trial. The first step is a non-comparative randomized phase II trial (power, 95%; one-sided alpha risk, 10%). Patients will be randomly assigned in a 1:1 ratio to adjuvant systemic FOLFOX (control arm) or adjuvant HAI oxaliplatin plus systemic LV5FU2 (experimental arm). A total 114 patients will need to be included. The main objective of this trial is to evaluate the potential survival benefit of adjuvant HAI with oxaliplatin after resection of at least 4 CRLM (primary endpoint: 18-month hepatic recurrence-free survival rate). We also aim to assess the feasibility of delivering at least 4 cycles of HAI (or i.v.) oxaliplatin after surgical treatment of at least 4 CRLM, the toxicity (NCI-CTC v4.0) of adjuvant HAI plus systemic chemotherapy, including HAI catheter-related complications, compared to systemic chemotherapy alone, and the efficacy of adjuvant HAI on hepatic and extra-hepatic recurrence-free (survival and overall survival).

**Discussion:**

If 18-month hepatic recurrence-free survival is greater than 50% in the experimental arm, the study will be pursued in phase III, for which the primary endpoint will be 3-year recurrence-free survival rate. Patients randomized in the phase II will be included in the phase III, with an additional number of 106 patients.

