### Statistical considerations

#### Required number of patients

The phase II is based on a two-step optimum Simon design [52] for the experimental arm, with the same number of patient in the control arm. The control arm allows checking that patients included are comparable to those included in previous studies that led to build study hypotheses, and to expand this study in a Phase III study by using a phase II-III design, depending on the study results.

The hypotheses are the following:18-months hepatic RFS rate with the control treatment of 30%18-months hepatic RFS rate with the experimental treatment of 50%A minimum follow-up time of 18 months for patient alive without recurrence.

With this hypothesis and to have a 95% power (beta risk = 5%) and a one-sided alpha risk of 10%, a total of 108 patients will have to be randomized. Since 5% of patients will be non-evaluable, a total of 114 patients will be included. The rate of non-evaluable patient will be monitored and if necessary an increase in sample size will be proposed. After the inclusion of the first 30 evaluable patients, an analysis on safety and feasibility after 6-month follow-up will be performed and reported to the independent data monitoring committee (IDMC).

An interim efficacy analysis in both arms will be performed after the inclusion of the first 30 evaluable patients with a minimum of 18-month follow-up in the experimental arm as planned by the Simon design. This analysis will be reported to the IDMC. Among the first 30 evaluable patients in the experimental arm,If 7 on the experimental arm or fewer patients were free of hepatic recurrence at 18 months, the Phase II will be stopped because of poor efficacy and the trial will be stopped.If 8 or more patients on the experimental arm were free of hepatic recurrence at 18 months, the Phase II will continue and the Phase III (or its activation) will be continued.

After evaluation of 18-month RFS in 54 evaluable patients,if 20 or less patients out of the 54 of the experimental arm were free of hepatic recurrence, the trial will stop because of poor efficacy.Otherwise, the conclusion will be that the 18-month RFS is good enough to continue or open to accrual the Phase III study.

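### The abstract makes an 18-month hepatic RFS above 50% the condition for phase III, while the statistical section sets the threshold at 21 of 54 (38.9%) and uses 50% as the target rate

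*Protocol article*

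**What the plan says.** The protocol article describes the move from phase II to phase III in two places.

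- **Abstract, Discussion paragraph:** "If 18-month hepatic recurrence-free survival is greater than 50% in the experimental arm, the study will be pursued in phase III". No denominator, count or interim stage is given, and no other go criterion appears in the abstract.
- **Statistical considerations, Required number of patients:** a two-stage Simon design for the experimental arm. At the interim look, "If 7 on the experimental arm or fewer patients were free of hepatic recurrence at 18 months", the trial stops; "If 8 or more patients on the experimental arm were free of hepatic recurrence at 18 months, the Phase II will continue". At the final look, the trial stops "if 20 or less patients out of the 54 of the experimental arm were free of hepatic recurrence". The text then adds: "Otherwise, the conclusion will be that the 18-month RFS is good enough to continue or open to accrual the Phase III study".

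The same section lists the design hypotheses: an 18-month hepatic RFS rate of 30% with control and 50% with the experimental treatment. It states 95% power and a one-sided alpha of 10%, and the Methods/Design paragraph of the abstract repeats both figures.

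**The concern.** The two places put different numbers on one decision. More than 50% of 54 patients means at least 28. The statistical section needs only 21. The abstract appears to have taken the rate that the design is powered to detect and used it as the bar for the observed result.

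This decision determines whether a further 106 patients are enrolled and whether superiority is tested at all. If the observed result fell between the two thresholds, a reader of the abstract would see a missed criterion, or one lowered afterwards, although the statistical section prespecifies that result as a go. A go criterion should have one value that anyone can check.

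**Working it through.** **Inputs (Required number of patients, unless noted)**
- Null rate p0 = 0.30; target rate p1 = 0.50.
- Stage 1: 30 evaluable experimental patients, stop at 7 or fewer.
- Final look: 54 evaluable experimental patients, stop at 20 or fewer.
- Stated power 95%, one-sided alpha 10%, 108 patients, 114 after allowing for 5% non-evaluable.
- Abstract condition: hepatic RFS above 50%. The abstract gives no denominator, so n = 54 is an assumption here, with 57 (half of 114) as the alternative.

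**Formula.** With X1 the number free of hepatic recurrence among the first 30, and X the number among all n,

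P(go | p) = Σ over x from 8 to 30 of P(X1 = x) × P(X2 ≥ c − x),

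where X1 ~ Bin(30, p), X2 ~ Bin(n − 30, p) and c is the final count needed for a go.

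**Step 1: reproduce the plan's figures.** 108 / 0.95 = 113.7, which rounds up to 114. With n = 54 and c = 21:
- power at p = 0.50: 96.1% (stated 95%);
- type I error at p = 0.30: 10.2% (stated 10%, exceeded by 0.2 points).

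The stated operating characteristics therefore belong to the 21/54 rule.

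**Step 2: convert both thresholds to counts.** 21/54 = 38.9% and 20/54 = 37.0%. Since 27/54 is exactly 50%, a result above 50% needs 28 or more. The two rules differ for every result from 21 to 27 of 54 (38.9% to 50.0%).

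**Step 3: apply the abstract condition as a decision rule**, keeping the 7/30 interim.

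| Final rule | P(go) at 30% | P(go) at 50% |
|---|---|---|
| ≥ 21/54 (statistical section) | 10.2% | 96.1% |
| ≥ 28/54 (above 50%) | 0.06% | 44.6% |
| ≥ 27/54 (if read as at least 50%) | 0.16% | 55.4% |
| ≥ 29/57 (above 50%, 57 patients) | 0.08% | 50.0% |

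**Step 4: how often the rules would disagree.** At a true rate of 50% and n = 54, 0.961 − 0.446 = 0.515. In about half of trials in which the treatment performs exactly as planned, the result would satisfy the statistical section but not the abstract. At a true rate of 60% the abstract rule would reach 91% power, so a bar of 50% suits a treatment well above the planned effect.

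**The case against.** A reader might infer that phase III opens only if the rate exceeds 50%, so that 21 to 27 of 54 is a stop under the abstract. The document does not say that. The sentence has the form of a sufficient condition and gives no stop rule; literally, it is silent on that range. This objection stands, and the contradiction depends on reading the sentence as the decision rule. That is still the natural reading, because it names an arm, a number and a consequence, and it is the only go criterion in the abstract.

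A reader might also infer that the trial really has 45% power instead of 95%. That is not supported either. The 95% is attached to the Simon design, whose rule delivers it. The 45% describes a hypothetical rule built on n = 54 and a simple proportion. The Statistical analysis plan section analyses phase II on all randomized patients, so about 57 per arm is equally arguable and gives 50%.

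Finally, the operative rule is hardly in doubt. The statistical section gives counts at both stages, the hypotheses and the error rates, and sends the interim analysis to the independent data monitoring committee. Nothing suggests that the abstract sentence would be applied in its place. This limits the practical risk but does not remove the mismatch in the published criterion.

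**Conclusion.** The point holds as an internal inconsistency in the decision threshold. The abstract's 50% is the target rate under the alternative hypothesis, and the threshold that matches the stated error rates is 21 of 54, together with the 7/30 interim rule. The thresholds are about 11 percentage points apart (50.0 − 38.9). If the abstract condition were used as the rule, power at the planned effect would be 45% to 50%, depending on whether 54 or 57 patients are counted, with a type I error below 0.1% in either case. These figures assume exact binomial counts with complete 18-month status and the interim rule kept as printed. They do not show that the phase II design is underpowered or that the two-stage rule is wrong on this point.

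**What to change.** Align the abstract sentence with the two-stage rule and keep that section's own outcome wording. For example: *The phase II continues if 8 or more of the first 30 evaluable experimental-arm patients are free of hepatic recurrence at 18 months, and the trial goes on to phase III if 21 or more of 54 are; 50% is the target rate under the alternative hypothesis, not the threshold.*

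Both stages should appear, because 21/54 alone is not the full rule. The outcome should stay as freedom from hepatic recurrence. Replacing it with freedom from a hepatic RFS event would change what is counted, since the endpoint definition under Secondary objectives also takes in death without recurrence.

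Cost: one sentence. No change to the sample size, analysis or error rates of the design.

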**Trial registration:**

ClinicalTrials.gov, NCT02494973. Trial registration date: July 10, 2015.

## Background

### Adjuvant chemotherapy

Approximately 20% of patients with colorectal cancer (CRC) present with liver metastases (CRLM) at the time of diagnosis of the primary, and another 20% will develop CRLM during follow-up [1–4]. Surgical resection of CRLM is the only chance of cure – ant the best chance of long-term survival – and yields 5-year overall survival (OS) rates of 30 to 40% [5–7]. However, up to 60% of patients relapse following surgery, with recurrence confined to the liver in half of the cases [8, 9], even despite the administration of perioperative [10, 11] or adjuvant [12–15] chemotherapy.

A pooled analysis of two randomized trials (278 patients) comparing systemic 5-fluorouracil (5FU)-based adjuvant chemotherapy with no chemotherapy after complete resection of CRLM demonstrated a trend towards increased disease-free survival (DFS) for patients receiving chemotherapy (27.9 vs. 18.8 months; *p* = 0.095) [12]. In addition, in one of these trials, adjuvant chemotherapy was an independent favorable factor for DFS [13]. The EPOC trial studied the administration of FOLFOX chemotherapy versus no treatment before and after liver resection in patients with one to three colorectal liver metastases. In that trial, a significant disease-free survival benefit was observed in the treated group (per-protocol analysis), but not in the intention-to-treat analysis [10, 11].

### Hepatic arterial infusion of chemotherapeutic agents

Hepatic arterial infusion (HAI) has been developed to ensure greater local concentration of cytotoxic agents, since liver metastases derive most of their blood supply from the hepatic artery, while normal liver tissue is primarily perfused by the portal vein. Thus, HAI achieved significantly higher tumor response rates compared to systemic chemotherapy, as shown by several randomized studies in patients with unresectable CRLM [16–24].

Several different chemotherapeutic agents have been administered via HAI in the treatment of CRLM [25]. Fluorodeoxyuridine (FUDR) is mainly used for HAI because of its short half-life (< 10 min) and extensive first-pass extraction by the liver (94–99%) [26]. However, its biliary toxicity limits its administration. To improve the tolerance and efficacy of HAI with FUDR, the addition of steroid agents in the hepatic artery (in order to reduce biliary toxicity) and of cytotoxic drugs (e.g., irinotecan, oxaliplatin) systemically has been developed [27, 28].

The alternative is the use of HAI of more recent molecules. In this field, HAI with oxaliplatin had the most important development, mainly in France. We reported that HAI oxaliplatin accumulates in liver metastases with a tumor/normal parenchyma concentration ratio of 4.3 and a significant decrease in total platinum and ultrafiltrable platinum [29], suggesting potential benefit of the HAI route in terms of tolerance (e.g., peripheral neuropathy) and efficacy. HAI oxaliplatin also exhibited a liver extraction ratio of 0.47 [30]. After a Phase I trial conducted in Germany, we have shown in a multicenter Phase II trial that HAI oxaliplatin and systemic 5FU-folinic acid (LV5FU2 regimen) induced a response rate of 64% (95% CI: 44–81%) and a median overall survival of 27 months (survival at 1 and 2 years: 82 and 63%, respectively) in 28 patients with unresectable CRLM in the first line (*n* = 7) or second-line (*n* = 21) setting [31]. The combination was well tolerated with main toxicity consisting of grade 3 (*n* = 8) or 4 (*n* = 2) neutropenia and severe pain during the administration of oxaliplatin (*n* = 6).

More recently, we showed that the addition of HAI oxaliplatin to systemic chemotherapy succeeded in converting unresectable CRLM to resectable lesions in 24% of patients, with a complete pathological response rate of 19% in the patients who underwent surgery [32].

### Adjuvant HAI of chemotherapeutic agents

Since the majority of recurrences occurs in the liver, adjuvant HAI chemotherapy is an option after resection of CRLM. Several randomized studies have compared adjuvant HAI of chemotherapeutic agents to fluoropyrimidine-based systemic chemotherapy or to surgery alone, with conflicting and somewhat outdated results [33–41]. Specifically, DFS and/or hepatic DFS have been demonstrated to be superior with adjuvant HAI as opposed to systemic chemotherapy in five of the ten randomized studies performed to date. In these studies, FUDR was the main chemotherapeutic agent used for HAI. Kemeny et al. [36] reported the results from a single-institution study in which 156 patients were randomized to postoperative HAI with FUDR plus systemic 5-FU ± leucovorin vs systemic therapy alone. An increase in two-year survival rate for the combination therapy group was observed as compared with the control group (90% vs. 60%, *p* < 0.001). The liver relapse-free survival was also significantly increased in the combination therapy group. Furthermore, an updated analysis with a median follow-up of 10.3 years reported a significantly greater DFS rate (31.3 vs. 17.2 months, *p* = 0.02) and a trend toward improved OS (68.8 vs. 58.8 months, *p* = 0.10) in the combined therapy group compared to the control group [42]. In a more recent study, House et al. retrospectively analyzed 250 patients who underwent resection of CRLM between 2001 and 2005 and received either adjuvant HAI FUDR combined with systemic chemotherapy (FOLFOX or FOLFIRI regimen) or adjuvant systemic chemotherapy alone. The 5-year liver-recurrence free survival (RFS), overall RFS, and OS in the HAI group were 77, 48, and 75%, respectively versus 55, 25, and 55% in the systemic chemotherapy alone group (*p* < 0.01). The multivariate analysis also revealed adjuvant treatment with HAI plus systemic therapy as an independent factor for longer DFS (*p* < 0.01) [43]. Recently, the results of a phase II study (NCT00268463, NSABP–C-09) assessing the potential benefit of systemic oxaliplatin and capecitabine alternating with HAI of FUDR after resection of CRLM have been reported [44]. The primary end point was 2-year survival. Fifty-five of 76 eligible patients were able to initiate protocol-directed therapy and completed median of six cycles (range, one to six). Three postoperative or treatment-related deaths were reported. Overall, 88% of evaluable patients were alive at 2 years. With a median follow-up of 4.8 years, a total of 30 patients had disease recurrence, 11 involving the liver. Median disease-free survival (DFS) was 32.7 months. In conclusion, alternating HAI FUDR and systemic capecitabine and oxaliplatin met the prespecified end point of higher than 85% survival at 2 years and was clinically tolerable.

### Adjuvant HAI of chemotherapeutic agents in high-risk patients

The hepatic intra-arterial route requires more technicality than the venous route and should be reserved to patients at high risk of developing hepatic recurrence after resection of CRLM. In order to select these patients more at risk, based on the different prognostic scores [45–50], the factor common to all these scores and simple to establish, is the number of resected CRLM greater than or equal to 4.

We retrospectively analyzed 98 patients at high risk of hepatic recurrence (≥4 resected CRLM) treated postoperatively with either HAI oxaliplatin plus systemic 5-FU (*n* = 44) or ‘modern’ systemic chemotherapy (FOLFOX or FOLFIRI) (*n* = 54) [51]. Adjuvant oxaliplatin-based HAI chemotherapy was feasible, with more than four cycles of HAI administered in 84% of the patients (average number of HAI cycles, 8.0 ± 1.7). The 3-year hepatic DFS rate was significantly longer in the HAI group compared to the i.v group (49% vs. 21%, *p* = 0.0008), as was the 3-year DFS rate (33% vs. 5%, *p* < 0.0001). In multivariate analysis, adjuvant HAI chemotherapy and R0 resection margin status were the only independent prognostic factors for prolonged DFS. This study suggests that HAI oxaliplatin is feasible and significantly improves DFS in patients at high risk of hepatic recurrence after resection (or thermal ablation) of CRLM. The observed DFS benefit is sufficiently substantial to challenge the current standard of treatment and to warrant confirmation in a randomized trial targeting patients selected for their high risk of hepatic recurrence. To date, no randomized study has compared adjuvant HAI chemotherapy to ‘modern’ (i.e. oxaliplatin- or irinotecan-based) systemic chemotherapy while taking into account the risk of liver recurrence.

We believe that adjuvant HAI oxaliplatin after resection of high-risk CRLM is the ideal setting for implementing HAI techniques. Firstly, HAI oxaliplatin is administered in a 2-h infusion every 2 weeks – like via the i.v. route – compared to a 14-day infusion every 5 weeks with FUDR. Secondly, HAI oxaliplatin rarely causes chronic biliary toxicity, unlike FUDR.

Currently, no adjuvant study with HAI in the adjuvant setting is ongoing. HAI oxaliplatin plus systemic LV5FU2 has shown activity as first-line palliative treatment of CRLM. This raises the question whether this treatment could be of value as an adjuvant treatment after CRLM resection.

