### Study population

This study will include patients after R0/R1 resection and/or thermal ablation of at least 4 CRLM (histological confirmation for at least one metastasis) without extrahepatic disease (except ≤3 lung nodules < 10 mm on chest CT scan deemed amenable to curative-intent resection/ablation).

Patients to be included in the study must fulfill the following inclusion criteria: histologically confirmed stage IV CRC, curative-intent R0/R1 resection (or thermal ablation) of at least 4 CRLM, preoperative oxaliplatin- and/or irinotecan-based chemotherapy +/− non-experimental biological therapy (e.g., anti-EGFR or antiangiogenic agent), confirmed radiological tumor control before surgery (i.e., objective response or stable disease according to RECIST1.1), age > 18 years, good health status (WHO performance status 0–1), adequate hematological function (absolute neutrophil count > 1.5 × 10^9^/l, platelets > 100 × 10^9^/l, hemoglobin > 9 g/dl), adequate liver function (serum bilirubin < 1.5 x ULN; alkaline phosphatase and transaminases < 5 x ULN), serum creatinine < 1.5 x ULN, informed consent signed by the patient or his/her legal representative, no pregnancy or breast feeding, adequate contraception in fertile patients, adequate private or national insurance coverage. Exclusion criteria include: extrahepatic tumor disease (except ≤3 lung nodules ≤10 mm on chest CT scan deemed amenable to curative-intent resection/ablation), symptomatic primary tumor requiring urgent surgery, contraindication to fluoropyrimidines or oxaliplatin, disease progression under oxaliplatin (including early hepatic relapse (less than 6 months) after end of adjuvant FOLFOX following primary tumor resection), history of any HAI treatment (chemotherapy, radioembolisation…), peripheral neuropathy> grade 1, history of cancer within 5 years prior to entry into the trial other than adequately treated basal-cell skin cancer or in situ carcinoma of the cervix, concomitant medications/comorbidities that may prevent the patient from receiving study treatments, patient already included in another clinical trial with an experimental molecule, patients unable to undergo medical monitoring test for geographical, social or psychological reasons.

An asymptomatic primary tumor is not a non-inclusion criterion if its resection is planned (reverse strategy allowed).

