### Treatment schedule

Randomization will be either performed during surgery, or within 6 weeks after surgery using web-based procedure (TenAlea®). Adjuvant chemotherapy must begin within 8 weeks after surgery. Patients will be randomly assigned using minimization procedure in a 1:1 ratio to:Arm A (control arm): adjuvant systemic (i.v.) chemotherapy (FOLFOX) administered every 14 days:Oxaliplatin 85 mg/m^2^ in 2 h IV day (D)1,Folinic acid 400 mg/m^2^ in 2 h IV (concomitantly to oxaliplatin) D1, followed by5FU bolus 400 mg/m^2^ in 5–10 min IV D1 followed by5FU 2400 mg / m^2^ IV in 46 hArm B (experimental arm): adjuvant HAI chemotherapy plus systemic chemotherapy (LV5FU2) administered every 14 days:Oxaliplatin 85 mg/m^2^ in 2 h HAI D1,leucovorin 400 mg/m^2^ in 2 h IV (concomitantly to oxaliplatin) D1, followed by5FU bolus 400 mg/m^2^ in 5–10 min IV D1 followed by5FU 2400 mg / m^2^ IV in 46 h

Randomization will be stratified according to the following factors:Tumor response to preoperative chemotherapy (objective response vs. stable disease)Number of resected CRLM (4–8 vs. > 8)Center

Patients will receive adjuvant chemotherapy (HAI or systemic) for a maximal duration of 6 months and at least 3 months for the postoperative period. The minimal duration of chemotherapy (pre- and postoperative period) will be of 6 months. Before starting adjuvant chemotherapy, CT scan of the abdomen, pelvis and chest and serum tumor markers will be done (within 4 weeks before starting adjuvant chemotherapy). In both arms, continuation of targeted therapy (if any) used in the preoperative treatment will be allowed.

The HAI catheter will be placed before initiating treatment, either surgically or percutaneously by interventional radiology and bound to an implantable port. Angiographic and/or scintigraphic verification of the HAI catheter functionality will be done within 28 days before the start of treatment. HAI chemotherapy should be performed by physicians and nurses familiar with this technique.

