For the Phase III, the primary endpoint will be 3-year recurrence-free survival (RFS) rate. Patients randomized in the Phase II will be included in the Phase III. The hypotheses are the following:3-year RFS rate with the control treatment of 15%3-year RFS rate with the experimental treatment of 30%, (HR 0.63)

With this hypothesis (α- risk, 5% (two-tailed); β- risk, 20%), the corresponding number of patients is 204 patients (152 events). With an increase of 7–8% (ineligible patients etc.…), the total number of patient is: 220 (164 events), i.e. 110 patients/arm, including 106 additional patients in the Phase III.

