#### Statistical analysis plan

The phase II analysis will be conducted on all the patients registered and randomized, in “intention to treat”. A second analysis will be conducted on the “treated” population, determined according to the treatment actually administered (per protocol analysis). The phase III analysis will be performed according to intent-to-treat principle, i.e. on all patients randomized. A minimum follow-up of 18 months for the last enrolled patient will be required.

The results for the primary and secondary endpoints will be presented by arm with a confidence interval at 95% (Rothman for survival data). Compliance data will be reported by number of cycles. The total dose of 5-FU (overall and according to its modalities: (bolus, continuous perfusion) by square meter, as well as the total dose of oxaliplatin (overall and according to its modalities: IA and IV) and the type and dose of target therapy if any will be described. The corresponding dose-intensity will be computed. Information on the treatment of recurrence will be also collected. Safety data will be reported according to their frequency and by system organ class. Analysis per patient (maximum grade) and per cycle will be reported. The proportion of patient with at least one grade 3 or more toxicity will be computed. For overall survival, survival rates at 12 and 24 months and median will be calculated. For hepatic and overall RFS, rates at 12 and 18 months and median will be calculated. Pattern of recurrences will be also described. As the trial is constructed as a phase II, no statistical test will be made.

The analysis on the 3-year RFS, the primary endpoint for the phase III, will be performed once the number requested of events will be reached and a median follow-up of at least 3 years observed. A long-term follow-up analysis with a minimum follow-up of 3 years and a median follow-up of at least 5 years will be also performed. Main endpoint and secondary efficacy endpoint will be compared by logrank test and reported with a hazard ratio and its 95% confidence interval. Data on compliance and safety will be compared by Wilcoxon or Chi^2^ test as appropriate.

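### The phase III RFS comparison does not use resection margin, which the protocol's own series reports as the only independent DFS factor besides HAI; adjusting for it would gain some power and protect against chance imbalance

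*Protocol article*

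**What the plan says.** All of this is in the protocol article.

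- *Study population*: the inclusion criteria accept "curative-intent R0/R1 resection (or thermal ablation) of at least 4 CRLM", so the population is mixed on margin by design.
- *Adjuvant HAI of chemotherapeutic agents in high-risk patients*: in the sponsor's retrospective series of 98 patients with at least four resected metastases, "adjuvant HAI chemotherapy and R0 resection margin status were the only independent prognostic factors for prolonged DFS". No hazard ratio for margin and no R1 share is reported.
- *Treatment schedule*: "Patients will be randomly assigned using minimization procedure in a 1:1 ratio". The listed factors are "Tumor response to preoperative chemotherapy (objective response vs. stable disease)Number of resected CRLM (4–8 vs. > 8)Center". Margin is not among them. On timing, "Randomization will be either performed during surgery, or within 6 weeks after surgery using web-based procedure".
- *Statistical analysis plan*, for phase III: "Main endpoint and secondary efficacy endpoint will be compared by logrank test and reported with a hazard ratio and its 95% confidence interval". No stratification and no covariate is named.
- *Required number of patients*: phase III is sized on 3-year RFS of 15% against 30% (HR 0.63), two-sided 5%, 80% power. This gives 152 events in 204 patients, raised to 164 events in 220 patients.

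**The concern.** The protocol reports one patient characteristic as independently related to DFS besides the treatment under test. It admits patients on both sides of that characteristic, then uses it neither to form the groups nor to compare them. Stratifying the test by the three minimization factors would not deal with this, because margin is not one of them.

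Two things are at stake. By chance, one arm may receive more R1 patients, and an unadjusted hazard ratio would carry that difference. Also, when a covariate predicts outcome, a test that conditions on it usually has more power than one that does not, and the planned power is only 80%. If adjustment is added after results by arm are known, it will look data-driven.

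**Working it through.** **1. The plan's own figure.** Under proportional hazards, HR = ln(0.30)/ln(0.15) = 1.2040/1.8971 = 0.6346. Schoenfeld's formula with 1:1 allocation gives events = 4(1.960 + 0.842)²/(ln 0.6346)² = 31.40/0.2068 = 151.8, so 152. This matches the plan. Inflation also reproduces: 204 × 1.08 = 220.3. With 164 events, power is Φ(0.4547 × √164/2 − 1.96) = Φ(0.95), about 83%.

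The 15% and 30% are whole-arm rates, so 0.6346 is a marginal hazard ratio, already averaged over R0 and R1. The stated sample size therefore fits an unadjusted test.

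**2. Assumptions.** The documents do not give the R1 share or the margin hazard ratio. I take R1 at 20–50% and the margin hazard ratio at 1.5–2.5.

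**3. Chance imbalance, 110 per arm.** The SD of the between-arm difference in R1 share is √(p(1−p) × 2/110).

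| R1 share | SD (points) | Chance of a difference of 10 points or more |
|---|---|---|
| 20% | 5.4 | 6% |
| 30% | 6.2 | 11% |
| 40% | 6.6 | 13% |
| 50% | 6.7 | 14% |

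The shift in the unadjusted log HR is roughly the difference in R1 share × ln(margin HR). For 10 points and a margin HR of 2, this is 0.10 × 0.693 = 0.069, a factor of 1.07. The standard error of the log HR at 164 events is about 2/√164 = 0.156, so the shift is about 0.44 of a standard error.

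**4. Power with and without margin.** Simulated trials had 204 patients and were cut at 152 events. Times were exponential within margin group and calibrated so that whole-arm 3-year RFS is 15% and 30%. There were 4,000 runs per setting (simulation standard error about 0.6 points).

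| R1 share | Margin HR | Treatment HR within margin group | Power, plain log-rank | Power, stratified by margin |
|---|---|---|---|---|
| 20% | 1.5 | 0.629 | 0.819 | 0.822 |
| 20% | 2.0 | 0.619 | 0.812 | 0.836 |
| 20% | 2.5 | 0.610 | 0.821 | 0.864 |
| 30% | 1.5 | 0.627 | 0.822 | 0.827 |
| 30% | 2.0 | 0.613 | 0.831 | 0.856 |
| 30% | 2.5 | 0.599 | 0.822 | 0.882 |
| 50% | 1.5 | 0.625 | 0.829 | 0.835 |
| 50% | 2.0 | 0.607 | 0.829 | 0.876 |
| 50% | 2.5 | 0.587 | 0.854 | 0.919 |

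The gain runs from 0.3 points (0.822 − 0.819) to 6.5 points (0.919 − 0.854). With no treatment effect, both tests rejected in 4.1–5.8% of runs, so type I error is near 5% either way.

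**The case against.** **No figure is wrong and validity is intact.** This stands. Randomization protects the unadjusted test, and its confidence interval already allows for chance imbalance.

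**A reader might infer that omitting margin leaves phase III underpowered or biases the hazard ratio toward 1.** The documents do not support this. It requires 0.635 to be read as the effect within margin groups. On that reading, simulation at 164 events with a margin HR of 2.0 gives 78–79% power unadjusted against 81–83% adjusted. But the plan derives its HR from whole-arm rates. Calibrated to those rates, the plain log-rank reaches 0.81–0.85 in every setting above. The gap between the two hazard ratios is one between marginal and conditional effects, not a bias in the planned comparison.

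**A reader might infer that the wrong minimization factors were chosen.** The article does not list which variables entered the series' multivariate model, so it cannot be said that response or lesion count was tested and failed. Lesion number has its own rationale: the article calls it the factor shared by the published prognostic scores.

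**A reader might infer that margin should be a minimization factor.** Allocation may take place during surgery, when final pathology is normally not available, and ablated lesions have no resection margin. Leaving margin out of the minimization is defensible.

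**A fuller plan may add an adjusted analysis.** It may; the article condenses the protocol, and the point holds for the text at hand. It is still worth raising because the article states a specific method without margin while reporting margin as prognostic.

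**The evidence for margin is thin.** It is one retrospective series of 98 patients, on DFS, with no effect size. That is why the gain is given as a range starting near zero.

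**Conclusion.** The point holds as an improvement in efficiency and balance for phase III, and no more than that. The population is mixed on margin, the protocol's own series reports margin as prognostic, and the stated comparison does not use it. With R1 at 20–50% and a margin hazard ratio of 1.5–2.5, both assumed, adjustment adds about 0 to 7 points of power. At the same R1 shares, a 10-point or larger R1 imbalance has a 6–14% chance, and a 10-point imbalance moves the treatment hazard ratio by about 7% if the margin hazard ratio is 2. If margin matters little, adjustment gains almost nothing. The 152 and 164 events, the 80% power and the type I error need no change.

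**What to change.** Record final margin status from the index operation in three categories: R0, R1 and ablation only. Prespecify it, together with the minimization factors, as a covariate or stratum in the phase III RFS analysis, and report the unadjusted log-rank and hazard ratio as well. Fix this before any phase III results by arm are seen.

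The cost is small. Because eligibility accepts both R0 and R1, it does not by itself require telling them apart, so this is one additional recorded item. Ablation-only patients need their own category, and the plan should say how patients with both resection and ablation are classed. For patients allocated during surgery, the record should confirm that resection was complete before allocation, so that margin is a pre-randomization variable. The sample size and the randomization procedure stay as they are.
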